**3.6 Other Outcome Variables**

- Proportion of negative RDT cases which receive ACTs from CHW or another malarial treatment from another source.
- Proportion of negative RDT cases with fast breathing and treated for pneumonia.
- Proportion of children with fast breathing whose symptoms and signs resolve without antibiotics.
- Proportion of children with pneumonia referred who comply with referral within 24 hours
- Proportion of children who experience adverse events attributable to the use of RDTs, such as severe bruises, skin infections, and prolonged bleeding following finger pricks
- Proportion of sick children correctly classified by CHW
- Proportion of sick children prescribed appropriate treatment for malaria/pneumonia according to the treatment algorithm
- Proportion of children treated for malaria/pneumonia who experience adverse events
- Proportion of drug and/or RDTs supply properly accounted for (consistency between stock in hand from stock summary forms and stock consumed based on consultation/treatment forms)
- Proportion of caretakers who take children to a CHW or health facility within 24/48 hours of onset of fever and or cough/difficult breathing.

.

**4.0 METHODS**

# 4.1 Study Site

The study will be conducted in the Chikankata Health Services area covering parts of Siavonga and Mazabuka Districts, which are located in the Southern Province of Zambia. The estimated population of the area is 70,000. The people of Siavonga and Mazabuka are Tonga.

The area is a typical rural area with poor road networks. Some parts of the area are inaccessible particularly during the rainy season as streams cut off some villages for at least two months of the year. Only two towns in the area are connected to the national power grid. The area has one hospital, the Chikankata Hospital with a hospital affiliated health center and five rural health centers (RHCs), two in Siavonga district and three in Mazabuka district. The hospital is owned by the Salvation Army Church and the RHCs by the government. Some of the RHCs do not have the full complement of staff (clinical officer, environmental health technician, nurse, and midwife). The rural health facilities are on average 30 kilometers away from Chikankata Hospital. Most services at the hospitals and RHCs are free, including all services for under-fives and pregnant women.

Data from the DHMTs show that the leading causes of death for children under five in the area are malaria, malnutrition, pneumonia, and diarrhea21,22 Malaria has consistently been the number one cause of consultation at all levels of health care in the area. The incidence of malaria in under fives, over the last few years ranges from 900 to 1200 per 1000 of the under five population. Similarly, the incidence of pneumonia and respiratory tract infections (non-pneumonia) is 70 to 80 per 1000 and 500 to 600 per 1000 respectively.

CHS is actively running a Primary Health Care (PHC) program which has a mobile and outreach services unit. The Mobile and Outreach Services unit support and supervise the RHCs and a number of community based workers, which include traditional birth attendants, community based distributors who distribute family planning devices, community nutrition demonstrators and the CHWs. The community-based workers normally work together and operate from a community health post structure built by the community.

There are 49 trained CHWs manning 43 community health posts in the area and supported by CHS. The initial CHW training lasted for twelve weeks, which included six weeks of classroom work and six weeks of practical. The responsibilities of the CHW involve treating minor illness including uncomplicated malaria, disease prevention, health education and community sensitization and mobilization, especially for outreach services. They work within the catchment area of health facility. They are supervised and supported by the mobile and outreach team of the PHC and staff of the RHCs. Most of the CHWs collect their community health worker kits monthly from Chikankata Hospital but a few collect from the supervising RHC. They submit monthly returns to Chikankata and the RHC on a specially designed form “CHW: Village Health Center Monthly Aggregation”. This form collects aggregated information on diseases seen, referrals to rural health centers and hospital, births, deaths, drug and material supply and consumption. There is no diagnosis of pneumonia listed on the form.

There is no formalized incentive package for the CHWs but CHS provides some incentives from time to time when resources are available. Such incentives include bicycles, umbrella and stationery. They also receive some incentives from the communities. These incentives are mostly in-kind and include items such as eggs, maize, and chickens. The community also assists them by organizing help for them on their farms and household tasks. Attrition rate of the CHWs is very low. The Chikankata Community Health Program follows the guidelines provided in the Zambia MOH reference manual for CHW “Community Health Workers Handbook” in running its program.

There are also neighborhood health committees (NHCs). These are groups of community-selected members who help manage community health services at the community level and hold community meetings to link people and health care providers. The chairpersons of these NHCs make up health centre committee (HCCs) that help in planning health activities and support the management of RHCs. In addition to these community groups, there are care and prevention teams (CPTs) formed in the wake of the Human Immunodeficiency Virus (HIV) /Acquired Immunodeficiency Syndrome (AIDS) epidemic who assist people infected and affected by HIV/AIDS. They also support referral, nutrition supplementation, care and support of the sick.

# 4.2 Study design

The study will be a cluster-randomized controlled trial. A study cluster will be defined as the catchment area of a community health post. CHWs work from a community health post with well defined catchment area and population within a health facility catchment area and are supervised by the staff of the health facility. The clusters (community health post catchment area) will be matched in pairs according to the health facility catchment area they belong to, the distance from the health facility and the population size. Randomization will then be done from among the matched clusters to select the intervention and the control arms. CHWs in both the intervention and control arms will receive training in the assessment and classification of children presenting with fever and/or cough/difficult breathing. The CHWs in the intervention arm will be supplied with RDTs, Coartem® and amoxicillin. The intervention CHWs will be trained to use RDTs in patients with reported fever and provide those with a positive result with Coartem while patients suspected of pneumonia (based on fast breathing) will be treated with amoxicillin as per the standard of care at health facilities and monitored. Those with negative RDT result will be treated with antipyretic and asked to return if they do not get better after 48 hours or condition deteriorates. In the control group, no RDT will be performed. The CHWs will be supplied with Coartem to treat malaria/febrile illness as per the IMCI guidelines and patients suspected of pneumonia will be referred to the health facility for treatment as per the current practice. The supply of the drugs and RDTs will come through the normal MOH sources. The study will utilize specialized field workers (data collectors and data supervisors) to visit CHWs to collect data on their consultations and follow-up children treated by CHWs. Consent will be sought from caregivers to allow us collect data by which to assess the effectiveness of the intervention. Caregivers in both the intervention and control arms are not obliged to receive care from the CHWs. They are free to go to any of the health facilities in the study area instead of a CHW. The study will collaborate with the MOH and the DHMTs to ensure that the health facilities in the study area have RDTs, Coartem and amoxicillin.

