**3.2.1 Primary Objectives**

- To determine whether the integrated management of malaria and pneumonia by CHWs at the community level increases the proportion of children under five years old who receive early and appropriate treatment for pneumonia as compared to children referred to health facility.
- To determine the extent, to which the use of RDTs by CHWs reduces the use of Coartem® in the management of children with acute fever, compared with management based on clinical criteria only.

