### Study Population and Recruitment

### Children between six months and five years who present to a CHW at the community health post with fever and/or cough/difficult breathing will be assessed, classified and managed. Six months was selected as the cut off because Coartem® is not recommended for younger children weighing less than 5 kg and also because of the difficulty of assessing very young children for pneumonia. Children outside this age range and adults will be managed according the current treatment guidelines for CHWs and will not be followed up by study personnel. Any child with severe illness or signs of severe malaria or pneumonia will be referred as per standard of care and excluded from enrollment into this study.

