### Present to CHW with cough or difficult breathing

### *Exclusion criteria:*

Children with any one or more of the following conditions will be excluded:

- Age below 6 months or above 5 years
- Presence of signs and symptoms of severe illness
  - Convulsions
  - abnormally sleepy or coma
  - persistent vomiting
  - unable to drink or feed
  - chest in-drawings
  - severe pallor
- Known sensitivity to Coartem® and/or amoxicillin

The CHWs will keep register of all patients seen as part of standard care. From this register, the CHWs will extract information to complete identification and baseline form for every child with fever or/and fasting breathing. This form will be used by data collectors to locate patients for the follow-up visits and also to measure the accuracy of classification and appropriateness of treatment.

In the intervention arm, children 6 months to 5 years whose caregivers refuse RDT testing will not be followed up. However, we will keep track of them and measure the proportion of RDT refusals.

The option for a caregiver to go to a health facility to receive care in place of being cared for by the CHW is an accepted norm in the communities. However, existing community based health educators in the area (NHCs, child survival facilitators, community based distributors, traditional birth attendants, growth monitors) in their interaction with community members will emphasize that they have this option.

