#### 4.14 Follow-up

The patients seen by the CHWs with fever and/or fast breathing will be followed up at home by the data collectors to assess the outcome of the treatment given or recommended. The follow-up visit will occur 5-7 days after the visit to the CHW. The data collectors will make contacts with CHWs at least every other day to take particulars of children treated from the identification and baseline forms in order to schedule a follow-up visit. During the follow-up visits, the data collectors will interview the caregiver (the person who took the child to see the CHW or in his/her absence a family member who knows sufficiently about the illness and the care received); and perform some basic examination including taking of temperature and counting of respiratory rate. Information that will be collected during the follow-up visits will include, complaints that prompted heath seeking at the CHW, treatment given, counseling or advice given, referrals, self-reported adherence to the medication, outcome of the visitation, alternative treatment after the visit and where such alternative treatment was obtained and current general condition and complaints. They will also be asked questions to explain inappropriate treatment. If a subject is found not to be improving, the data collector will advise the caregiver to go to the clinic.

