#### 4.16 Counseling and Community education

CHWs will provide counseling and basic health information to their patients during consultation. The counseling will include the need to return if condition deteriorates or the child experiences any adverse effects of the treatment. In addition, the CHWs in collaboration with the existing community based health educators in the area: NHCs, CPTs, child survival facilitators; community based distributors; traditional birth attendants and growth monitors will provide basic health information to the communities. Elements of such messages will include:

- General danger signs requiring immediate referral to a health facility
- Symptoms of pneumonia and malaria requiring assistance from the CHW, including danger signs
- Need to use the services of the CHWs
- Importance of adhering to counseling and instructions
- Information about taking the drugs themselves, side effects, need to take with food
- Preventive measures to be used with regard to malaria and pneumonia

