#### Routine data collected from CHWs and facility-based records.

#### Performance assessments of CHW skills.

#### Follow-up visits of children treated by CHWs at home.

#### A set of household surveys.

CHWs will keep an outpatient department (OPD) register in which each person attended to will be registered. The OPD register will provide information on the name of the patient, address, sex, age or date of birth, date of onset of illness, main complaints, classification of the disease, drugs given, and comments (recovered, referred or died). The CHW will then make a monthly summary of the register. In addition, the CHW will keep a daily tally sheet for drugs and supplies dispensed and make a monthly summary. The CHW will keep a record of referred cases. The record (which is supplemented by information received from the health center) will include date and time of referral, presenting signs and symptoms (diagnosis), date and time seen at referred centre, date of discharge, and final diagnosis. The CHW will also complete an “identification and baseline form” for every child between six months and five years with fever or fast breathing. The health facilities in the area will keep morbidity and mortality records including information on all CHW referrals.

On a monthly basis the data collectors will visit the CHW and health facility and collect summaries of records kept in special design case report forms (CRFs). The information collected on CRFs for CHWs will include number of children seen, those classified as malaria or pneumonia or both, RDTs performed, drugs dispensed, referrals and whether a supervisory visit was made The information that will be collected on CRF at the health facility will include number of malaria and pneumonia cases, severe malaria and pneumonia cases, referrals from CHWs, deaths by cause, availability of RDTs, Coartem**®** and amoxicillin.

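### Primary outcome 1 is measured only in children who come to a CHW, and who comes can differ by arm after randomisation; the direction of any bias is uncertain

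*Protocol*

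**What the plan says.** **Who is counted.** Under Study Population and Recruitment, entry is limited to "Children between six months and five years who present to a CHW at the community health post with fever and/or cough/difficult breathing". Section 4.14 limits outcome assessment in the same way: "The patients seen by the CHWs with fever and/or fast breathing will be followed up at home by the data collectors".

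**The other route to care.** Section 4.2 says of caregivers in both arms: "They are free to go to any of the health facilities in the study area instead of a CHW". The text after the exclusion criteria adds that community-based health educators "in their interaction with community members will emphasize that they have this option". Section 4.16 also lists a message that pulls the other way: "Need to use the services of the CHWs".

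**What differs by arm.** Under section 4.2, intervention CHWs give amoxicillin for suspected pneumonia and control CHWs refer to the facility. The study works with the health authorities to keep facilities supplied with amoxicillin (4.2, 4.11). Facility care is free for under-fives (4.1).

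**What is claimed.** The first primary objective (3.2.1) asks whether the intervention "increases the proportion of children under five years old who receive early and appropriate treatment for pneumonia". The sentence goes on to name children referred to a health facility as the comparison. The outcome clock starts at onset of illness (3.4).

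**What facilities record.** The listed contents of the facility form (5.1) include "number of malaria and pneumonia cases, severe malaria and pneumonia cases, referrals from CHWs, deaths by cause", plus stock availability. Health post of residence, onset date and whether a CHW was seen first are not listed. The facility data capture system is still to be developed (4.8).

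**The concern.** The unit randomised is the catchment, but the children compared are selected later by their caregivers' choice of provider. The option to bypass the CHW is offered equally in both arms; the reason to use it is not equal. For a child with suspected pneumonia, the control CHW is a stop on the way to the facility, whereas the intervention CHW is the place of treatment. Section 4.15 has the design explained to community leaders and the information passed on to the wider communities, so caregivers may well know what their post offers.

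A child taken straight to a facility is in neither the numerator nor the denominator of primary outcome 1. If the share or the type of such children differs between arms, the two groups of CHW attenders are no longer the groups that randomisation made comparable. Intention-to-treat analysis (6.1) covers only children in the data. Pair matching on distance (4.2) balances clusters, not who attends within them. The GEE model (6.1) adjusts only among enrolled children. No stated analysis of primary outcome 1 would show whether this had happened.

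**Working it through.** **1. The plan's own figure.** Section 4.3 gives 50% vs 70%, 80% power, two-sided alpha 0.05 and, in the last row, a coefficient of 0.25 with 12 children per cluster. The Hayes-Bennett matched-pair formula, with the tabulated coefficient entered as a between-cluster coefficient of variation, gives per arm

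2 + (1.960 + 0.842)² × [0.25/12 + 0.21/12 + 0.25² × (0.50² + 0.70²)] / 0.20² = 2 + 7.849 × 0.08458 / 0.04 = 18.6, rounded up to 19.

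That is 38 clusters and 38 × 12 = 456 children; 456 × 1.15 = 524.4, stated as 524. The figure reproduces, and the present point does not change it. The planning rates of 50% and 70% are carried forward.

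**2. Effect of direct attendance on the observed difference.** The protocol gives no rate of direct attendance and no timeliness for direct attenders, so both are assumed over a range. Let b be the share of control children with pneumonia who go straight to a facility, and s the proportion of those treated early and appropriately. Assume 50% success over all control children, 70% over all intervention children, and no direct attendance in the intervention arm. Then

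observed control rate = (0.50 − b·s) / (1 − b), and shift in the difference = b(s − 0.50) / (1 − b).

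Example: b = 20%, s = 70% gives (0.50 − 0.14)/0.80 = 45%, so the observed difference is 70 − 45 = 25 points.

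Observed difference in points (true value 20):

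| b | s = 30% | s = 50% | s = 70% | s = 90% |
|---|---|---|---|---|
| 10% | 17.8 | 20.0 | 22.2 | 24.4 |
| 20% | 15.0 | 20.0 | 25.0 | 30.0 |
| 30% | 11.4 | 20.0 | 28.6 | 37.1 |

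The sign depends only on whether s is above or below the control average of 50%. Because that average mixes direct attenders and CHW attenders, this is the same as asking whether direct attenders do better or worse than control CHW attenders.

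**3. Under no true effect.** With 50% in both arms and b = 20%, the same formula gives a spurious difference of 0.20 × 0.20 / 0.80 = 5 points at s = 70% and 0.20 × 0.40 / 0.80 = 10 points at s = 90%. At s = 30% it gives −5 points.

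**4. Could the household surveys fill the gap?** They include women whether or not they used a CHW (5.1). Inputs: 420 caregivers per round (4.3); pneumonia incidence 70 to 80 per 1,000 under-fives, read as annual (4.1); assumed 1.5 under-fives per household and one month of recall. Expected cases per round: 420 × 1.5 × 0.07/12 = 3.7 to 420 × 1.5 × 0.08/12 = 4.2. The stated 420 equals 20 households × 21 posts. If 20 were taken at each of 42 posts, the count would double to 7.4 to 8.4. Either way there are too few cases to re-estimate the outcome by arm.

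**The case against.** The strongest reply is that the intended population is CHW-managed children. The objective names children referred to a facility as the comparison, and the hypothesis in 3.2.2 places the gain among CHWs trained to treat both diseases. This stands as a reading of the target, although the 50% planning rate in 4.3 is worded for children in general. It does not restore comparability, because CHW attenders can still be differently selected in each arm.

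Second, the mechanism may be weak. Caregivers would have to suspect pneumonia before choosing a provider, yet section 2 says its symptoms overlap heavily with those of malaria. Malaria is far more common (900 to 1,200 vs 70 to 80 per 1,000, 4.1), and control CHWs stock Coartem, so families of febrile children still have reason to attend. Communities are also told to use CHWs. All of this limits the likely size; none of it makes attendance independent of arm.

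Third, a reader might infer that the effect will be overstated. The documents do not support that. Many facilities are hard to reach (2, 4.1) and the clock runs from onset, so direct attenders could be treated later than control CHW attenders, which reverses the sign.

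Fourth, a reader might try to size the bias by applying 50% and 70% to CHW attenders and, say, 75% to direct attenders. With 20% or 40% direct in control and 10% in intervention, the intervention rate is 0.9 × 70 + 0.1 × 75 = 70.5% and the control rates are 55% and 60%. The differences are 15.5 and 10.5 points instead of 20. But equal direct attendance in both arms already gives 71 − 55 = 16.0 and 72 − 60 = 12.0 points. So 4.0 of the 4.5 and 8.0 of the 9.5 points come from changing the target population, not from selection by arm. Those figures are not the true effect.

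Finally, some relevant data are planned: the household surveys, and timely care-seeking at a CHW or facility (3.6). They can help show whether care-seeking differs by arm. They are not linked to primary outcome 1, and the 3.6 measure combines the two routes.

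**Conclusion.** The point holds as a risk of selection by arm after randomisation in primary outcome 1, left unmeasured by the analyses stated. A bias in favour of the intervention is plausible, since direct attenders skip the referral step and facilities are to be stocked, but the direction is uncertain. The protocol has no data to size it. Under the assumptions shown (no direct attendance in the intervention arm, 10 to 30% in control), the shift in a 20-point effect runs from −8.6 points at 30% success among direct attenders to +17.1 points at 90%, and is zero at 50%. These are illustrations, not estimates. The conclusion that needs no assumption is that the trial, as planned, could neither detect nor bound the bias.

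**What to change.** On the facility data capture form still to be developed (4.8, 5.1), record for each child of 6 months to 5 years with pneumonia: health post of residence, whether a CHW was seen first, date of onset, and drug and course dispensed. Report the number of direct attenders per cluster by arm, alongside care-seeking by arm from the household surveys.

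Keep the CHW-attender analysis as primary. Pre-specify a sensitivity analysis of primary outcome 1 over all care-seeking children, by cluster of residence. Use the same outcome for direct and CHW attenders: timing, drug and course as dispensed. Otherwise home-verified adherence in one group would be set against dispensing records in the other. State in advance that the conclusion will be qualified if the two analyses disagree. Do not let an observed difference in attendance decide which analysis is primary; that would be a data-dependent switch.

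Cost: a few form fields, one more analysis, and possibly an ethics notification, because the follow-up consent in section 7 covers children treated by CHWs. Direct attenders will have no home-verified adherence, and children who seek no care remain outside both analyses. Randomisation, care and sample size are unchanged.
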